## Introduction

Preterm birth, defined as birth before 37 weeks of gestation, is a leading cause of child morbidity and mortality. According to the World Health Organization, ~13 million babies are born preterm each year globally, which equates to more one premature birth for every ten deliveries. Specifically, in Nordic countries, the prevalence of preterm birth is estimated to be around 5.8%. Due to rapid advancements in obstetrics and neonatal care, most of these preterm babies have a better survival rate; however, they are more prone to cognitive deficits and neurodevelopmental disorders, such as ADHD, which exerts a heavy burden on affected families, society and to the health care system.

Preterm birth is associated with poor cognitive abilities. However, studies so far have mainly focused on children born very preterm (< 32 weeks of gestation) or extremely preterm (< 28 weeks of gestation), even though children born moderate to late-preterm (32 – 36 weeks of gestation) make up a substantial proportion of preterm birth groups. Compared to those born at term, children born moderate to late preterm are more prone to acute morbidity conditions such as respiratory distress, temperature instability, and neonatal hypoglycaemia. Despite this, these babies have been overlooked by the perinatal community, with extensive research mainly focused on children born extremely/very preterm. Recent evidence suggests that those born moderate-to late preterm and early-term, also at high risk of cognitive difficulties compared to their term born peers, yet studies have produced inconsistent results. For example, some studies have shown lower cognitive functioning in the moderate-to late preterm group during childhood, while others have shown no differences.

In general, cognitive abilities is largely heritable, with heritability estimates reaching upto 70%. Interestingly, the heritability of general cognitive abilities increase significantly from childhood to early adulthood. Prior studies focusing on contribution of the heritability and biological risk factors, such as preterm birth, have mostly adopted familial designs. Previous studies using sibling analysis have investigated the association between gestational age and intelligence quotient (IQ), finding that these associations are independent of shared familial confounders and statistical covariates. While these studies provide initial insight into the effect of biological risk factors, such as preterm birth, accounting for genetic mechanisms underlying with IQ, they have several limitations. First, these designs require assumptions that can sometimes be violated, for example, siblings do not necessarily share 50% of their genes, nor do they necessarily inherit same risk alleles. Second, this approach cannot account for specific environmental effects, such as maternal factors. Therefore, distinguishing environmental factors and conducting separate genotyping would identify specific environmental contributions, which could be targets for improving cognitive outcomes.

81 Previous familial design studies focusing on association between gestational age and IQ, have  
82 primarily focused on general cognition and have not explored individual domains. It is known that  
83 children born preterm show delay in cognitive abilities, but majority of these children perform within  
84 normal range for general cognitive functioning as a group (i.e., they perform 0.5 - 1.0 SD below that  
85 of term-born peers). But, specific functions such as attention, working memory, and processing  
86 speed are often delayed in this cohort, have not been explored.

87  
88 In addition, preterm birth is a syndrome where various causes might act synergistically to its  
89 manifestation. Previous systematic and meta-analyses have assessed numerous non-genetic risk  
90 factors for preterm birth, such as obstetric and medical history, environmental exposures, and  
91 postnatal factors. Exploring the independent contribution of these risk factors on cognitive abilities  
92 could pave the way for risk-specific interventions and enhance our understanding of the mechanisms  
93 related to these outcomes.

## Study objectives

The aims of this study are two-fold:

- Investigate the association between preterm and early-term births on cognitive outcomes during mid-childhood; and assess the extent to which these associations can be explained by unmeasured genetic and environmental factors.
- Investigate the association between weeks of gestation and cognitive outcomes during mid-childhood; and assess the extent to which these associations can be explained by unmeasured genetic and environmental factors.

## Hypothesis

Children born preterm is independently associated with poor cognitive abilities, with larger effect size for lower gestational ages.

## Methods

### Participants

The neuroimaging and behavioural data used in this study will be obtained from the ABCD Study (data release 5.0; <https://abcdstudy.org/>; <http://doi.org/10.15154/1523041>), a longitudinal cohort of 11,875 children born between 2005 and 2009. These children were enrolled at ages 9-11 years from 21 research sites across the U.S. between 2016 and 2018, with the intention of following them for a period of at least 10 years. This recruitment cohort closely matches the sociodemographic composition of the US population of 9-11-year-old children. Most of the children were enrolled through local elementary and charter schools at each data-collection site. A smaller portion was recruited through community outreach and word-of-mouth referrals outside of the school setting. Twins were identified and recruited from birth registries.

During each visit, children accompanied by a parent/guardian, completed a series of measures. These included neurocognitive tests, mental and physical health questionnaires, environmental exposure data collection, providing biological specimens, and participating in brain imaging. All were asked for an in-person assessment session for self- or parent-report of mentioned behavioural measures and for biological specimen collections once a year, with brain imaging conducted biannually. For this study, we will use data collected between 2016 and 2018.

Children were excluded if they were born extremely preterm (< 28 weeks of gestation) or had birth weight (< 1200 g), were not proficient in English, had any neurological problems, had a history of seizures, or had a contraindication to undergo brain MRI scans. All children and their parents/guardians provided informed written consent/assent for participation, and the central Institutional Review Board at the University of California, San Diego approved the study protocols. All the research methods were performed in accordance with the relevant guidelines and regulations.

### Neurocognitive measures

The neurocognitive battery was designed to be completed in 70 min. Participants first completed the Snellen vision chart as a measure of visual acuity. Legal blindness (with vision correction) was a study exclusion.

A brief handedness inventory, consisting of four self-report questions, was also administered.

The neurocognitive testing battery, comprised of ten measures, was then initiated. All tests were administered using an iPad with one-on-one monitoring by a research assistant. The neurocognitive

battery consists of seven different tasks that cover episodic memory, executive function, attention, working memory, processing speed, and language abilities, and was normed for samples between the ages of 3 and 85 years. The total administration time for the NIH Toolbox Cognitive battery is approximately 35 min.

The Toolbox Picture Vocabulary Task measures language skills and verbal intellect. The Toolbox Oral Reading Recognition Task is a reading test that asks individuals to pronounce single words. The Toolbox Pattern Comparison Processing Speed Test is a measure of rapid visual processing. The Toolbox List Sorting Working Memory Test requires participants to use working memory to sequence task stimuli based on category membership and perceptual characteristics. The Toolbox Picture Sequence Memory Test was modelled after memory tests asking children to imitate a sequence of actions using props. The Toolbox Flanker Task, a variant of the Eriksen Flanker task, is a response inhibition/conflict monitoring task that measures the ability to modulate responding under congruent versus incongruent stimulus contexts. The Toolbox Dimensional Change Card Sort Task measures cognitive flexibility. Each of the Toolbox tasks produces several scores, some of which are adjusted based on participant demographics. All tasks provide raw scores, uncorrected standard scores, and age-corrected standard scores.

Age corrected task scores will be used in our analyses.

## Rey auditory verbal learning test

The Rey Auditory Verbal Learning Test (RAVLT) measures auditory learning, memory, and recognition. A customized automated version, created through the Q-interactive platform of Pearson assessments was used. This test requires participants to listen to and recall a list of 15 unrelated words over five learning trials. Following initial learning of the list, a distractor list of 15 words is presented, and the participant is asked to recall as many words from this second list as he/she is able. Next, recall of the initially learned list is assessed. Recall following a 30-min delay (during which participants engage in other non-verbal tasks), permits longer term retention to be assessed.

## Little man task

This task engages visual-spatial processing, specifically mental rotation, with varying degrees of difficulty. The task involves the presentation of a rudimentary male figure holding a briefcase in one hand in the middle of the screen. The figure may appear in one of four positions: right side up vs. upside down and either facing the respondent or with his back to the respondent. The briefcase may be in either the right or left hand. Respondents indicate by button press which hand is holding the briefcase.

182  
183

## 184 Outcomes

### 185 Primary outcome

- 186 ➤ Cognitive composite scores

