### 187 Secondary outcomes

- 188 ➤ Domains of cognitive scores

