## Statistics

Maternal and child characteristics will be summarized using means and standard deviations for continuous variables and frequencies with counts for categorical distributions. To compare the demographic and clinical characteristics between children born preterm, early-term and born at full-term, independent samples t-test and  $\chi^2$ /Fisher exact tests will be employed. Missing covariates will be imputed through multiple imputations by chained equations with the predictive mean matching method using the MICE package in R.

Hierarchical logistic/linear regression model will be used to investigate the relationships between preterm birth and behavioural/brain outcomes. Model 1: Adjusted for age of child, sex, SES, Polygenic scores, 20 PCs, and scanner sites; Model 2: Model 1 + Maternal factors; and Model 3: Model 2 + Neonatal factors; Model4: Model 3 + child factors

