### **Primary analyses:**

- Linear regression model will be used to investigate whether the one-factor (intelligence) differ between preterm birth, early-term birth and full-term birth (presented as standardized beta and 95% CI)

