### **Secondary analyses:**

- Linear regression model will be used to investigate whether the general cognitive abilities, executive functions, and working memory performance differ between preterm birth and full-term birth (presented as standardized beta and 95% CI)

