### **Exploratory analyses:**

Sex and birthweight

Primary analysis will be uncorrected with statistical significance at 0.05. Secondary analysis will be adjusted for multiple comparison corrections.

All analysis will be carried out using R studio.

242 **Planned Figures and Tables**

243 Table 1 Demographics of maternal and child characteristics

244 Table 2 Results from the primary analysis

245 Table 3 Results from the weeks of gestation

246

247 Figure 1 Results of PCs.

248 Figure 2 Outcomes

249

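### The primary outcome carries two labels that do not match, and no deciding contrast or model is named, although the primary analysis is left uncorrected at 0.05

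*SAP*

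**What the plan says.** **Outcome.** Under Outcomes, the whole entry for the primary outcome is "Cognitive composite scores", and the whole entry for the secondary outcomes is "Domains of cognitive scores". Under Primary analyses the text reads "Linear regression model will be used to investigate whether the one-factor (intelligence) differ between preterm birth, early-term birth and full-term birth". Under Secondary analyses the question is "whether the general cognitive abilities, executive functions, and working memory performance differ between preterm birth and full-term birth".

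**Model.** The opening of the Statistics section states: "Hierarchical logistic/linear regression model will be used to investigate the relationships between preterm birth and behavioural/brain outcomes". It then lists four nested models. Model 1 has age, sex, SES, polygenic scores, 20 principal components and site. Models 2, 3 and 4 add maternal, neonatal and child factors in turn. None is called the primary model.

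**Exposure.** The Exposures section lists five gestational-age categories. The Primary analyses sentence uses three groups. Study objectives adds weeks of gestation as a second aim, and the analysis sections place it neither with the primary nor with the secondary analyses.

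**Error rate.** The rule stands after the heading Exploratory analyses: "Primary analysis will be uncorrected with statistical significance at 0.05". The secondary analyses are to be corrected for multiple comparisons.

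**The concern.** Testing a primary analysis at 0.05 without correction is sound when there is exactly one primary test. This SAP does not define one.

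The two places that carry the word primary do not describe the same variable: one is a plural, unspecified set of composites, the other a single factor with no derivation. A third score of overall ability sits among the secondary analyses with nothing to tell it apart from the factor. The status of an overall-ability result, and whether it is corrected, therefore depends on a choice the document leaves open.

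The deciding comparison and the deciding adjustment set are open as well. The SAP's Participants section says that the data were collected in 2016 to 2018, and the appendix already reports derived quantities such as the share of variance captured by the SES component. With data already in hand, the written plan is the main protection against settling the score, contrast or model after results are seen.

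**Working it through.** **Step 1: is the primary variable fixed?** Side by side in the SAP:

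| Place | Label | Status | Derivation given |
|---|---|---|---|
| Outcomes, Primary outcome | cognitive composites (plural) | primary | none |
| Primary analyses | one factor, intelligence | primary | none |
| Secondary analyses | general cognitive abilities | secondary | none |

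The Neurocognitive measures section does not fill the gap. It refers to ten measures, then to seven tasks, and says that age-corrected task scores will be used; these are task scores, not composites. The Rey test and the Little Man task have their own sections, and nothing says whether they enter the composite or the factor. The Secondary outcomes entry covers domains only, so a general-ability score does not obviously belong there.

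**Step 2: is the deciding test fixed?** The Primary analyses sentence compares three groups. With full-term as reference that makes two contrasts. Neither is ranked first and no global test is named. Four models are listed and none is singled out.

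**Step 3: what does the uncorrected rule imply?** The inputs from the SAP are alpha = 0.05 and two contrasts against full-term. Sidedness is not stated; two-sided tests are assumed.

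- Plan's own figure, one test: 1 − (1 − 0.05)^1 = 0.05. The stated level is right for a single primary test.
- Two independent tests (upper figure): 1 − (1 − 0.05)^2 = 1 − 0.9025 = 0.0975.
- Two contrasts sharing the full-term group: under the null their correlation is r = √{[s1/(s0+s1)] × [s2/(s0+s2)]}, where s0 is the full-term share and s1, s2 are the other two. The SAP gives no shares, so two sets are assumed.
  - Equal thirds: r = √(0.5 × 0.5) = 0.50. The chance that at least one |z| exceeds 1.96 is about 0.091 by bivariate normal integration (0.090 in a simulation of 200,000 draws).
  - 60% full-term, 25% early-term, 15% preterm: r = √(0.25/0.85 × 0.15/0.75) = √0.0588 = 0.24. The chance is 0.096 by both routes.

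The result is therefore about 9 to 10% across these assumptions, close to double the nominal level.

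**Step 4: what restores 5%?** With three groups, one global test of the exposure at 0.05, with each contrast then tested at 0.05 only if the global test is significant, keeps the family-wise error at 0.05. If no groups differ, the global test gives the protection. If one group differs from another, at most one of the two contrasts against full-term can still be a true null, and it is tested at 0.05. A fixed order of contrasts also holds 5%. If both contrasts are to stand as co-primary, 0.025 each gives 1 − 0.975^2 = 0.0494.

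**The case against.** The best defence is that this is an observational cohort with one graded hypothesis: the Hypothesis section expects poorer cognition after preterm birth, with larger effects at lower gestational age. Preterm and early-term birth are then levels of one exposure, reported as standardized betas with 95% confidence intervals. The Primary analyses wording also permits a single three-level test, which would hold 5%, and the SAP says openly that the primary analysis is uncorrected. This stands in part. The excess error arises only if the two contrasts are tested separately, and the fault is that the SAP does not say which reading applies. A definition in a protocol not at hand would not cure it either, because the labels conflict within the SAP.

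A reader might infer more than the document supports:

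- *That the primary outcome has three names.* Only two labels are primary; general cognitive abilities is placed under Secondary analyses.
- *That general cognitive abilities is the same score as the one factor and should simply be deleted.* It may be, but it may also be one of three intended narrower scores. The SAP does not settle this.
- *That executive function or working memory could be promoted to primary.* The Secondary analyses section places them there, and their correction is required.
- *That the error rate is 18.5% or higher.* That figure needs four contrasts against full-term (1 − 0.95^4 = 0.1855). These come from the Exposures list, whereas the Primary analyses sentence speaks of preterm birth as one group. Figures above it also need several primary composites with assumed correlations, and the SAP names no such set.
- *That the four models multiply the error.* They are nested fits to the same data, so their estimates would be strongly correlated. The open choice of model is a fault, but no figure can be put on it here.

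**Conclusion.** The point holds. The two primary labels do not match, the factor that is to be tested has no derivation, an overall-ability score appears as secondary without being distinguished from it, and neither the deciding contrast nor the primary model is named. Combined with an uncorrected 0.05, this means that the stated level is not the chance of a false primary claim.

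The size is a family-wise error of about 9 to 10% for one outcome and one model. It rests on two-sided tests, on the two contrasts of the Primary analyses sentence each being tested at 0.05, and on assumed group shares, which matter little (9.0 to 9.6%, with 9.75% as the independent upper figure). If the sponsor intends one three-level test, the error is 5% and only the wording is missing. The conflict over the outcome remains either way and should be resolved before the exposure analyses are run.

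**What to change.** 1. Use one defined score under both Primary outcome and Primary analyses. State which tests enter it and how it is estimated, and build it without reference to gestational age.
2. Under Secondary analyses, say how general cognitive abilities differs from that score, or remove it if it is the same.
3. Designate one of Models 1 to 4 as the primary model and present the others as supporting.
4. Test the three-level exposure of the Primary analyses section once at 0.05 with a global test. Interpret preterm and early-term against full-term only if that test is significant, or test them in a stated fixed order. Step 4 of the working relies on there being three groups and does not carry over to all five exposure categories.
5. State whether the weeks-of-gestation analysis is primary or secondary. It should not silently replace the group comparison, which is a separate aim.

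The cost is SAP wording only, with no new data. The downside is that fewer results can be labelled primary.

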### 187 Secondary outcomes

- 188 ➤ Domains of cognitive scores

## 189 Exposures

190 Full-term 39 weeks of gestation and above

191 Early-term 37-38 weeks of gestation

192 Late-preterm 34 – 36 weeks of gestation

193 Moderate-preterm 32 – 34 weeks of gestation

194 Very preterm 28 – 32 weeks

195

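### The very, moderate and late preterm bands overlap at weeks 32 and 34, so any band-specific estimate rests on an unstated choice among four codings

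*SAP*

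**What the plan says.** The Exposures section is the SAP's only definition of the exposure groups. It lists five bands:

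- "Full-term 39 weeks of gestation and above"
- "Early-term 37-38 weeks of gestation"
- "Late-preterm 34 – 36 weeks of gestation"
- "Moderate-preterm 32 – 34 weeks of gestation"
- "Very preterm 28 – 32 weeks"

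It gives no rule for which endpoints are included, no convention for weeks plus days, and no rule for ties.

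The Introduction uses different limits. It describes "very preterm (< 32 weeks of gestation") and treats the next group as one block, "moderate to late-preterm (32 – 36 weeks of gestation"), without dividing moderate from late.

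The analysis sections do not name the five bands. Statistics and Primary analyses speak of preterm, early-term and full-term birth. Secondary analyses speak of preterm and full-term birth. The second aim in Study objectives concerns weeks of gestation, and Planned Figures and Tables reserves Table 3 for it.

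**The concern.** Groups that enter a regression as categories must be mutually exclusive. As listed, a child born in week 32 or week 34 qualifies for two groups, and the SAP does not say which one applies. Two analysts following the plan could build different very, moderate and late preterm groups from the same data and report different band estimates.

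The Introduction motivates the study by the lack of attention to moderate-to-late preterm children, and the moderate band is the one affected at both ends. The hypothesis is graded, with a larger effect expected the earlier the birth, so band estimates are one natural way to display it. A choice left open until the data are seen also weakens the value of a prespecified plan.

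**Working it through.** The SAP states no figure on this point, so there is none to reproduce. The check has four steps.

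**1. Assign each completed week to every band that contains it** (limits from Exposures; lower limit of 28 weeks from Participants).

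| Week | Bands |
|---|---|
| 28–31 | very |
| 32 | very and moderate |
| 33 | moderate |
| 34 | moderate and late |
| 35–36 | late |
| 37–38 | early-term |
| 39 and above | full-term |

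Weeks 32 and 34 are the only double assignments. Week 33 is the only week that belongs to moderate preterm alone.

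**2. Test whether one endpoint convention rescues the list.**

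- Both ends included: weeks 32 and 34 are in two bands.
- Upper end excluded throughout: the overlap goes, but weeks 36 and 38 fall in no band.
- Lower end excluded throughout: the overlap goes, but weeks 28 and 37 fall in no band.

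The 37–38 and 39-and-above bands fit together only as inclusive whole weeks, and that is the reading that produces the overlap.

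**3. List the possible codings.** Two weeks with two possible homes each give 2 × 2 = 4. Mean gestational age is the weighted mean Σ(w·rʷ)/Σrʷ over the weeks w in a band, where r is the ratio of births in one week to births in the week before. The values below take r = 1 (equal counts).

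| Week 32 to | Week 34 to | Very (mean) | Moderate (mean) | Late (mean) |
|---|---|---|---|---|
| very | moderate | 28–32 (30.0) | 33–34 (33.5) | 35–36 (35.5) |
| very | late | 28–32 (30.0) | 33 (33.0) | 34–36 (35.0) |
| moderate | moderate | 28–31 (29.5) | 32–34 (33.0) | 35–36 (35.5) |
| moderate | late | 28–31 (29.5) | 32–33 (32.5) | 34–36 (35.0) |

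Across the four codings the moderate mean moves by 33.5 − 32.5 = 1.0 week. With r = 1.3 it runs from 32.57 to 33.57, and with r = 1.6 from 32.62 to 33.62. The very preterm mean moves by 0.5 week at r = 1, by 30.51 − 29.82 = 0.69 at r = 1.3, and by 30.86 − 30.05 = 0.81 at r = 1.6. The late preterm mean moves by 0.5, by 35.57 − 35.17 = 0.40, and by 35.62 − 35.30 = 0.32 respectively.

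The Introduction's limit for very preterm removes the first two rows. It does not choose between the last two.

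**4. Illustrate how many children are concerned.** The values of r are assumptions. Counting from week 28, the share of weeks 32 and 34 among weeks 28–36 is (r⁴ + r⁶) / (1 + r + … + r⁸).

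- r = 1.2: (2.074 + 2.986) / 20.80 = 24.3%
- r = 1.3: (2.856 + 4.827) / 32.01 = 24.0%
- r = 1.5: (5.063 + 11.391) / 74.89 = 22.0%

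In all four rows of step 3 the three preterm bands together cover exactly weeks 28–36. A pooled preterm group, and the early-term and full-term groups, therefore contain the same children whichever coding is used.

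**The case against.** The strongest objection is that no named analysis is shown to use the three overlapping bands. The primary and secondary analyses are worded in terms of preterm birth as a whole, and the second aim works with weeks of gestation directly. Under those readings the overlap changes no estimate. This stands, and it limits the point to band-specific results. It does not remove the point: the SAP lists five exposure groups, never says that three of them will be pooled, and defines exposure nowhere else.

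A reader might infer that the primary result itself, or every group effect in the study, depends on how weeks 32 and 34 are coded. The documents do not support that, because both weeks are preterm under every coding. A reader might also infer that the graded hypothesis cannot be tested. That goes too far as well, since an analysis by week of gestation addresses it without bands.

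It can also be said that the Introduction already settles the matter. It does so for week 32, although the sentence describes earlier literature and the Exposures section contradicts it. It does not for week 34, because moderate and late are kept together there.

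Finally, the 22–24% is a share of children in two particular weeks. It is neither a misclassification rate nor a bias in a coefficient. The birth-weight exclusion (below 1200 g) could also thin the earliest weeks, so that a constant weekly ratio would not hold. All of this is accepted.

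**Conclusion.** The bands are wrong as written. Weeks 32 and 34 each fall in two groups, no single endpoint convention repairs the list, and the very preterm band disagrees with the Introduction. None of this depends on any assumption about the distribution of births.

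The consequence is confined to estimates for the very, moderate or late preterm bands, which depend on an unstated choice among four codings. Across those codings the mean gestational age of the moderate group moves by about one week. The size of any change in a coefficient cannot be derived, because the SAP gives neither weekly counts nor an expected effect per week.

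This should be fixed before analysis. It does not threaten a pooled primary contrast.

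**What to change.** Rewrite the three preterm bands in the Exposures section as mutually exclusive ranges of completed weeks:

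- Very preterm: 28–31, which agrees with the Introduction.
- Week 34: in one band only, stated explicitly. Moderate 32–33 with late 34–36 is one example. It is compatible with the Introduction but not dictated by it; moderate 32–34 with late 35–36 would be equally compatible.
- Early-term and full-term: unchanged.

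Add one sentence to Primary analyses saying whether the five bands or a pooled preterm group enter the model.

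The cost is two changed numbers and one sentence. No new data are needed.
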